#### Psychosocial analyses

With regard to the psychosocial measures, suitable numerical and graphical summaries (e.g. box plots, scatterplots and case profile plots) will be presented to summarise the within-subject (i.e. time) and between-subject (i.e. treatment group) factors.

Several analyses will be performed to compare the change in the psychosocial response variables across time and between groups. These will include linear mixed models initially, using baseline as a covariate and subsequently where the response variables will be expressed as changes from baseline. Different covariance structures will be compared in order to best model the correlation structure within subject.

An intention to treat analysis will be performed to compare the estimated effect of the psychosocial response variables when imputing values for all missing data to the results obtained when analysing the data while ignoring missing data.

Multiple imputations [26,27] will be performed using a Predictive Model Based Method where each missing value is replaced by 5 imputed values. The imputations will be generated via randomly drawn regression model parameters from the Bayesian posterior distribution based on the cases for which the imputation variable is observed.

An estimate of the difference in the mean response, for each of the psychosocial response variables of interest, when comparing those on the intervention to the controls, will be provided by pooling the results of each 'complete' model (i.e. with imputed values) using the Barnard-Rubin adjustment method [28]. The estimated coefficients, standard errors and p-values for the intervention to control comparison from the original and complete analyses will be reported for each of the psychosocial response variables in addition to the fraction of information about the coefficients missing due to non-response/non-attendance.

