### Randomisation and Patient Recruitment

In the study we used a cluster randomisation with the unit of randomisation being the participating DAFNE centre. There are 6 participating centres in this study and it was anticipated that each cluster would have approximately 75 participants each. We felt that DAFNE educators would not be able to separate the 2 approaches to follow-up if they were expected to deliver both. By randomising centres to deliver one or other method of follow-up we hoped to minimise or avoid contamination between the two arms of the study. The process of randomisation of centres was undertaken by a statistician not involved in the study and who was blind to the identity of the hospitals being randomised. The randomisation was done using a computer-generated table of random numbers.

Prior to the study each of the participating DAFNE centres used a similar approach to filling DAFNE courses. A waiting list was maintained of individuals with Type 1 diabetes attending the centre who had expressed an interest in receiving DAFNE training. Using this list, groups of approximately 50 patients were invited to attend a recruitment evening in which the DAFNE course was described and members of the DAFNE team were available to answer questions. A brief description of the study aims and objectives was included in the material presented at the recruitment evening. Individuals were asked to consider participating in the study but were not required to give an answer at the recruitment evening. Following the recruitment evening approximately 6 DAFNE courses (each comprising 8 participants) would be filled. Prior to the week of DAFNE training, individuals were invited to attend a pre-course assessment visit. During this visit a DAFNE educator would make sure that the individual met the inclusion criteria for the study. Informed consent was generally obtained at this visit and baseline study questionnaires were given to the patient.

Study Inclusion criteria:

1. At least 18 years of age at recruitment

2. Diagnosed with type 1 diabetes for at least one year

3. Attending the adult diabetes clinic in one of the participating centres

4. The ability to speak and read English

5. A willingness to monitor blood sugar levels at regular intervals

6. A willingness to transition to a basal/bolus insulin regimen prior to DAFNE training (if not already on such a regimen)

7. A glycosylated haemoglobin (HbA_1c_) level below 13 percent at recruitment.

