Participants in the intervention arm of the study are also seen at 6, 12 and 18 months. The 6 and 12 month visits are organised as group education sessions and build on the concepts of goal setting and action planning introduced during the original DAFNE course. A follow-up curriculum was developed to guide DAFNE educators involved in delivering these sessions and specific training in the delivery of this curriculum was given to all intervention arm DAFNE educators. Groups are encouraged to determine their own priorities and select from a range of DAFNE self-management skills review topics designed specifically for these follow-up sessions. The role of the DAFNE educator is to achieve a blend of a patient-centred and curriculum-centred approach to the session. Follow-up curriculum topics include HbA_1c _and targets, diary keeping and self-monitoring, principles of dose adjustment, carbohydrate calculation, hypoglycaemic management, exercise and physical activity, alcohol and sick day rules. An example of a typical timetable for a group follow-up session is outlined in Table 1. Where DAFNE graduates are unwilling or unable to participate in a follow-up session with their original group they are offered a follow-up session with a different DAFNE group from that centre. Every effort is made to avoid delivering follow-up on a one-to-one basis in this arm of the study. In keeping with an emphasis on quality assurance an external peer review of the delivery of one 6 month follow-up session in each of the 3 intervention arm centres will be undertaken during the study.

**Table 1 T1:** Typical timetable used during the intervention follow-up sessions

09:30	Welcome
09:40	HbA_1c _results, review of blood sugar and targets

10:10	Quiz to identify 3 areas the group would like to focus on (patient-centred approach)

10:20	Curriculum used to guide group-led discussion of identified topics

12:10	Goal setting and action planning

12:30	Close

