### Statistical Considerations

#### Sample Size

We used a sample size calculator designed for cluster randomised trials [25]. We based the sample size calculation on an anticipated HbA_1c _difference between the 2 arms of the study of 0.5 percent from month 6 onwards. This came from the observation in the UK study that DAFNE training led to a 1.0 percent drop in HbA_1c _at 6 months but reverted to 0.5 percent by 12 months [9]. Our study hypothesis is that group follow-up will be able to maintain the benefit out to 18 months. Unlike the UK DAFNE Study patients were not excluded with baseline HbA_1c _below 7.5 percent. Based on a standard deviation of HbA_1c _of 1.2 and an intra-class correlation co-efficient of 0.05 we estimated that 450 patients would be required to detect a 0.5 percent difference with 90 percent power.

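### Centres were randomised, but the psychosocial mixed models specify only within-subject correlation and name no centre-level term; carried out as written, their standard errors are too small

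*Protocol article*

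**What the plan says.** On the design, the protocol article is clear. Randomisation and Patient Recruitment describes cluster randomisation, with "the unit of randomisation being the participating DAFNE centre", and gives the numbers: "There are 6 participating centres in this study and it was anticipated that each cluster would have approximately 75 participants each". DAFNE and Study Interventions refers to external peer review of "one 6 month follow-up session in each of the 3 intervention arm centres", so the split is three centres against three. Sample Size, which concerns HbA1c, assumes "an intra-class correlation co-efficient of 0.05".

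Psychosocial analyses is the most detailed analysis text in the article. It plans linear mixed models, first with baseline as a covariate and then on change scores. On correlation it says: "Different covariance structures will be compared in order to best model the correlation structure within subject". For missing data it plans regression-based multiple imputation in which "each missing value is replaced by 5 imputed values", with results pooled "using the Barnard-Rubin adjustment method". Coefficients, standard errors and p-values for the arm comparison are to be reported for each psychosocial variable, with and without imputation.

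The section does not mention centre. Planned Analyses does list study centre among the adjustment variables, but only for the HbA1c analysis.

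**The concern.** The data have three levels: visits within patients within centres. The text specifies correlation at the lowest level and is silent on the level that was randomised. Patients in a centre share educators, and in the intervention arm the 6 and 12 month follow-up is delivered in groups, so some correlation within centre is to be expected. The authors' own sample-size assumption says as much for HbA1c.

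A model with visit and patient levels only takes the precision of the arm effect from about 450 patients, when it is limited by six centres. A chance difference between two sets of three centres could then be reported as an effect of group follow-up. The section covers several instruments (DSQOLS, PAID, HADS and EQ-5D), so the same error would be repeated across many tests.

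**Working it through.** **Inputs.** Six centres, three per arm, about 75 patients each (Randomisation and Patient Recruitment; DAFNE and Study Interventions). ICC 0.05, given for HbA1c (Sample Size). Assumed: psychosocial ICCs from 0.005 to 0.05, and two-sided testing at 5%, since no significance level is stated.

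**The plan's own figures.** 6 × 75 = 450 agrees with the stated sample size. The article gives no precision or error rate for the psychosocial analyses, so there is none to reproduce. As a side check on the ICC: a 0.5 difference with SD 1.2 and 90% power needs 122 per arm without clustering, and with a design effect of 4.7 about 1,148 in total, not 450. A total of 450 would correspond to an ICC of (225/122 − 1)/74 ≈ 0.011. That is a separate matter, but it is another reason to read the result over a range.

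**Step 1: one visit, centre left out.**
- Design effect (DE) = 1 + (75 − 1) × ICC
- True SE / reported SE = √DE
- Actual type I error = 2 × [1 − Φ(1.96/√DE)]

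| ICC | DE | SE ratio | Type I error at nominal 5% |
|---|---|---|---|
| 0.005 | 1.37 | 1.17 | 9.4% |
| 0.01 | 1.74 | 1.32 | 13.7% |
| 0.02 | 2.48 | 1.57 | 21.3% |
| 0.05 | 4.70 | 2.17 | 36.6% |

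These are two-sided rates. By symmetry about half of the false rejections favour the intervention: roughly 18% at ICC 0.05, 11% at 0.02 and 7% at 0.01.

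**Step 2: three follow-up visits.** Averaging a patient's visits removes within-patient noise but leaves the centre effect, so the problem grows. Take total variance 1, within-subject correlation ρ and a centre effect that is constant over visits. The patient mean then has within-centre variance (ρ − ICC) + (1 − ρ)/3. At ICC 0.05:
- ρ = 0.5: 0.45 + 0.167 = 0.617; ICC of the mean = 0.05/0.667 = 0.075; DE = 6.55; SE ratio 2.56.
- ρ = 0.7: 0.65 + 0.10 = 0.75; ICC of the mean = 0.05/0.80 = 0.0625; DE = 5.63; SE ratio 2.37.

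A simulation of 20,000 trials per setting gave type I errors of 45% and 42% for these two cases. At ICC 0.02 it gave 27% and 24%, and at ICC 0.01 17% and 16%. The values of ρ are assumptions.

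**Step 3: centre respected.** In the same simulations, a t-test on the six centre means with 6 − 2 = 4 degrees of freedom rejected in 4.8% to 5.1% of trials.

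**Step 4: why a fixed centre effect does not help.** Each centre belongs to one arm, so the arm indicator is the sum of three centre indicators. The arm effect is then aliased with centre and cannot be estimated separately. The HbA1c wording in Planned Analyses therefore cannot be carried over as a fixed effect.

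**Step 5: pooling.** The Barnard-Rubin method takes the complete-data degrees of freedom as an input, and the pooled value cannot exceed it. A patient-level model would supply several hundred; the arm contrast has about 4.

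**The case against.** The strongest reply is that this is silence in a condensed article. The sentence on covariance concerns the repeated-measures structure, which any mixed model here must choose. A linear mixed model can also hold a random centre intercept, and nothing in the section excludes one. The authors plainly knew of clustering: they used a cluster sample-size calculator and named centre for HbA1c. This stands as far as it goes. It rules out saying that the plan decides to ignore centre. It does not remove the point, because the section is specific on model class, covariance selection, imputation, pooling and reported quantities, and the only correlation it specifies is within subject.

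Four stronger readings are tempting, and the documents do not support them:
- *That the section defines its model by time and treatment group alone.* That phrase describes what the numerical and graphical summaries will show; it is not a model specification.
- *That the imputation omits centre.* No imputation predictors are listed, and no complete-data degrees of freedom are stated, so neither can be called wrong.
- *That the standard errors will be far too small in any event.* The 0.05 is for HbA1c. The psychosocial models adjust for baseline or use change scores, and the relevant ICCs are unknown. At 0.005 to 0.01 the error is real but moderate.
- *That five imputations are too few.* That has no bearing on clustering and forms no part of this point.

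These are also secondary outcomes.

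**Conclusion.** The point holds in conditional form. The psychosocial section specifies within-subject correlation only and commits to inference on an arm effect randomised across six centres. If it is carried out as written, standard errors are understated by a factor of about 1.2 at ICC 0.005 to 2.2 at ICC 0.05 for a single visit, with type I errors of about 9% to 37% at nominal 5%. With three visits averaged, the errors reach 42% to 45% at ICC 0.05 under the assumed within-subject correlations. The figures rest on 75 patients per centre, equal cluster sizes, two-sided 5% tests and an assumed range of psychosocial ICCs. The direction does not depend on the exact ICC: any positive value makes the standard errors too small. For imputation and pooling, the finding is only that the inputs are unstated and should be made consistent with the design.

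**What to change.** State in the psychosocial section that:

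1. every mixed model includes a random intercept for centre, alongside the planned within-subject covariance;
2. the arm effect is tested with Kenward-Roger or Satterthwaite degrees of freedom, about 4, or alternatively by a cluster-level analysis of centre summaries on 4 degrees of freedom. With six centres the estimated centre variance can fall to zero, so say in advance that the test does not then revert to patient-level degrees of freedom;
3. centre is not entered as a fixed effect in the models that estimate the arm effect;
4. the imputation model includes centre, by multilevel imputation or centre indicators, and the Barnard-Rubin complete-data degrees of freedom are set at about 4.

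No new data are needed. The cost is wider intervals. The critical value rises from 1.96 to 2.776 (t on 4 degrees of freedom), a factor of 1.42. Combined with the SE ratios for one visit, intervals are about 1.17 × 1.42 ≈ 1.7 times as wide at ICC 0.005 and 2.17 × 1.42 ≈ 3.1 times as wide at ICC 0.05. That width reflects what six centres can show on these secondary outcomes.

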**Methods:**

Six participating centres were cluster randomised to deliver either group follow-up or a return to traditional one-to-one clinic visits. In the intervention arm group follow-up was delivered at 6 and 12 months post DAFNE training according to a curriculum developed for the study. In the control arm patients were seen individually in diabetes clinics as part of routine care. Study outcomes included HbA_1c _levels, self-reported rates of severe hypoglycaemia, body weight and measures of diabetes wellbeing and quality of life. These were measured at 6, 12 and 18 months after recruitment. Generalisability (external validity) was maximised by recruiting study participants from existing DAFNE waiting lists in each centre, by using broad inclusion criteria (including HbA_1c _values less than 13 percent with no lower limit) and by using existing clinic staff to deliver the training and follow-up. Internal validity and treatment fidelity were maximised by quality assuring the training of all DAFNE educators, by external peer review of the group follow-up sessions and by striving for full attendance at follow-up visits. Assays of HbA_1c _were undertaken in a central laboratory.

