### Outcomes and Measurement

The primary outcome (on which sample size calculations are based) is the change in HbA_1c _between baseline and the 18 month follow-up visit. Patient-reported rates of severe hypoglycaemia (defined as a hypoglycaemic episode requiring the assistance of another person for treatment) will be reported as a secondary outcome along with change in weight and in psychosocial measures of wellbeing and quality of life.

Table 2 shows the measurement plan for the study. Because of the potential for inter-laboratory variation in the method and reporting of HbA_1c _results this outcome variable was assayed centrally. Blood was sent to the Royal Victoria Hospital in Belfast which has a track record of co-ordinating laboratory measurements for large scale studies. The method used was a DCCT-aligned HPLC assay (ADAMS-A_1c _HA-8160). Lipid levels were measured in the local laboratory in each hospital. License agreements were obtained for all questionnaires used in the study. The **Diabetes-Specific Quality of Life Scale (DSQOLS) **was originally developed in Germany [20] and is a quality of life measure specific for people with type 1 diabetes. It consists of 10 goal or preference items that are weighted to 10 satisfaction items resulting in a preference-weighted treatment satisfaction score. A further 57 items form 8 domains and are rated on a 6-point Likert scale with a total score reflecting quality of life. The domains are social relations, leisure time flexibility, physical complaints, worries about the future, diet restrictions, daily hassles, fear of hypoglycaemia and daily burdens & restrictions. For use in the Irish DAFNE Study the scale was altered slightly from the original to reflect linguistic differences and more culturally appropriate scale-items. These slight modifications did not alter the psychometric properties of the instrument [21]. The **Problem Areas in Diabetes (PAID) **measure is a 20 item questionnaire that uses a Likert-scale to assess an individual's diabetes-related distress [22]. The **Hospital Anxiety and Depression Scale (HADS) **is a dual instrument that uses 7 items along a Likert-scale to measure both anxiety and depression [23]. It is a suitable self-rating scale for anxiety and depression in patients with both somatic and diagnosed mental health issues with good reliability and responsiveness [24].

**Table 2 T2:** Data collections and follow-up intervals

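### Five imputations are valid but too few to give a stable fraction of missing information, or stable p-values if missingness is moderate, for the secondary psychosocial outcomes; raising the number is nearly free

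*Protocol article*

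**What the plan says.** The Psychosocial analyses section of the protocol article sets out multiple imputation in which "each missing value is replaced by 5 imputed values". The imputations come from "randomly drawn regression model parameters from the Bayesian posterior distribution", so each run depends on random numbers. The completed-data results are pooled "using the Barnard-Rubin adjustment method".

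The same section commits to specific outputs for every psychosocial variable: "The estimated coefficients, standard errors and p-values for the intervention to control comparison from the original and complete analyses will be reported", together with "the fraction of information about the coefficients missing due to non-response/non-attendance". The imputed results are to be set beside results that ignore the missing data.

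The Outcomes and Measurement section makes these measures secondary: severe hypoglycaemia "will be reported as a secondary outcome along with change in weight and in psychosocial measures of wellbeing and quality of life". Table 2 has the questionnaires completed at baseline, 6, 12 and 18 months. The article gives no expected amount of missing data. The nearest statement is in the Methods part of the abstract, which speaks of "striving for full attendance at follow-up visits".

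**The concern.** The number of imputations is a stated value, not a detail left for later, so it can be judged against the outputs that depend on it. Two of those outputs, the p-value and the fraction of missing information, use the variance between imputations. With 5 imputations that variance is estimated from 5 values, on 4 degrees of freedom.

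Two things are at stake. First, the fraction of missing information is what a reader would use to judge how much the imputation matters, and it could be far from its true value by chance. Second, the section is built on a comparison of imputed with non-imputed results. If the imputed p-value shifts noticeably with the random draw, a difference caused by the draw can be read as an effect of missing data.

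**Working it through.** **Inputs**
- Number of imputations m = 5, random Bayesian draws, Barnard-Rubin pooling: Psychosocial analyses.
- True fraction of missing information f: not in the article. Assumed 0.05 to 0.3.
- Complete-data degrees of freedom: not in the article. Taken as 440 (close to the 450 patients in Sample Size, individual-level analysis), with 4 as the opposite extreme (the 6 centres in Randomisation and Patient Recruitment, minus 2).
- Threshold 0.05, two-sided: assumed.

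The article gives no derivation of the 5, so there is no figure of its own to reproduce.

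**Step 1: precision of the between-imputation variance.** Its estimate is distributed as B × chi-square(m−1)/(m−1), so its coefficient of variation is sqrt(2/(m−1)).
- m = 5: sqrt(2/4) = 71%. The 95% range is 0.12 to 2.79 times the true value.
- m = 20: sqrt(2/19) = 32%.
- m = 50: sqrt(2/49) = 20%.

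These figures do not depend on how much is missing.

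**Step 2: the point estimate.** Relative efficiency is 1/(1 + f/m). At m = 5 it is 1/1.02 = 0.98 for f = 0.1 and 1/1.06 = 0.94 for f = 0.3. The Monte Carlo error as a share of the standard error is sqrt(f/m): sqrt(0.1/5) = 14% and sqrt(0.3/5) = 24%. The point estimate is thus affected less than the variance.

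**Step 3: p-value and fraction over repeated seeds.** Scale the total variance at unlimited m to 1, so U = 1 − f and B = f. For each seed, draw the pooled estimate from a normal distribution with variance B/m around its unlimited-m value, and draw the estimate b of B as in Step 1. Then:
- T = U + (1 + 1/m)b
- r = (1 + 1/m)b/U
- p-value from t with the Barnard-Rubin degrees of freedom ν
- reported fraction = (r + 2/(ν + 3))/(1 + r)

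Central 95% ranges over at least 100,000 seeds per setting, for a result with p = 0.05 at unlimited m and 440 complete-data df:

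| True fraction | m | p-value | Reported fraction |
|---|---|---|---|
| 0.1 | 5 | 0.025–0.106 | 0.02–0.30 |
| 0.1 | 50 | 0.040–0.063 | 0.07–0.14 |
| 0.2 | 5 | 0.016–0.154 | 0.04–0.51 |
| 0.2 | 50 | 0.036–0.070 | 0.15–0.27 |
| 0.3 | 5 | 0.011–0.202 | 0.06–0.65 |
| 0.3 | 20 | 0.024–0.101 | 0.18–0.45 |
| 0.3 | 50 | 0.032–0.078 | 0.23–0.39 |

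At a true fraction of 0.05 the p-value range is 0.031 to 0.082 with m = 5 and 0.043 to 0.058 with m = 50.

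**Step 4: a result away from the threshold.** If p is 0.02 at unlimited m, the chance that a seed reports p of 0.05 or more is:

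| True fraction | m = 5 | m = 20 | m = 50 |
|---|---|---|---|
| 0.1 | 3% | under 0.1% | under 0.1% |
| 0.2 | 14% | 0.3% | under 0.1% |
| 0.3 | 24% | 2% | under 0.1% |

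**Step 5: few degrees of freedom.** With 4 complete-data df, m = 5 and p = 0.05 at unlimited m, the p-value range is 0.036 to 0.089 at a true fraction of 0.1 and 0.019 to 0.177 at 0.3. With m = 50 it is 0.045 to 0.057 and 0.037 to 0.071. The ranges are narrower than at 440 df, but the pattern is the same. The fraction formula is then dominated by its small-df term, so the share of total variance due to missing data is the better guide: at a true 0.1 it ranges from 0.016 to 0.271 with m = 5 and from 0.068 to 0.139 with m = 50.

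**The case against.** The strongest reply is that 5 imputations is not an error. The Barnard-Rubin t reference already allows for a small m. At 440 df the simulated false-positive rate with m = 5 is 0.049 to 0.051 for true fractions of 0.05 to 0.4, and power of 90% under unlimited imputations becomes 89.0% at a fraction of 0.1. That stands. A reader might infer from the seed ranges that the planned inference is biased or invalid; the method the article describes does not support that. The fault is one of reproducibility.

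The p-value ranges are also centred on a result at exactly 0.05, where the verdict is most fragile. That stands too: even with m = 50, close to half of seeds fall on each side of 0.05 for such a result, so a larger m does not settle that case. Step 4 shows that the problem is not confined to it. Averaged over data under the null, however, the m = 5 verdict differs from the unlimited-m verdict in only 1.5% of trials at a fraction of 0.1 and 3.1% at 0.3.

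The amount of missing information is unknown. The trial strives for full attendance, and repeated measures with baseline as a covariate make some missing values predictable. If the fraction is low, the p-value effect is small. A flat statement that the p-values depend heavily on the seed therefore goes further than the article supports. The imprecision of the reported fraction does not need that assumption.

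Finally, the outcomes are secondary, the non-imputed result is reported alongside and needs no seed, and the section attaches no decision rule to the imputed p-value. All of this limits the weight of the point. A reader might also count the lack of a stated seed or Monte Carlo error report as a fault, or extend the point to HbA1c. The first is programming detail that an article commonly leaves to the full plan. As to the second, the imputation text covers only the psychosocial measures.

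**Conclusion.** The point holds as a cheap improvement to a secondary analysis. The conclusion about the fraction of missing information rests only on m = 5: the variance behind it has a coefficient of variation of 71% whatever the missingness, so the article promises a statistic that its own setting estimates poorly. The conclusion about p-values depends on an assumed fraction. The effect is modest at 0.05 to 0.1 and becomes material at 0.2 to 0.3, where a result with p = 0.02 under unlimited imputations would be reported at 0.05 or above for 14% to 24% of seeds. These figures assume 440 complete-data df; with 4 df the spread is smaller but still present. Validity, bias and the primary HbA1c analysis are not in question.

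**What to change.** In Psychosocial analyses, replace the 5 imputed values with a larger number: at least 20, preferably about 50. Fifty is a sensible choice and not a unique threshold. At a true fraction of 0.3, m = 20 already cuts the chance of a p = 0.02 result being reported at 0.05 or above from 24% to 2%, while m = 50 brings it under 0.1% and narrows the reported fraction to 0.23–0.39. The imputation model, the pooling method and the list of outputs can stay as they are. The cost is one number in the text and minutes of computing, with no extra data.
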